### Intervention

The intervention being evaluated is a structured cell phone initiative to improve communications between healthcare providers and patients. The intervention protocol was conceived in 2005 by several brainstorming meetings between health care provider staff at the clinics, and ultimately incorporated feedback from pilot patients from a survey and from small group sessions[3].

Every week, on Monday mornings, the site-clinician (typically a nurse or clinical officer) sends a text message (SMS) to all subjects in the intervention arm to remind them about their support and enquire into how they are doing. Typically, a slogan is used such as "Mambo?" which is Kiswahili for "How are you?", but similar slogans in other local languages can also be used at the clinicians' discretion. To simplify their work, the clinicians use the 'send to many' function on their cell phone for mass/group messaging. Intervention subjects are instructed to respond within 48 hours either that they are doing well ("Sawa") or that they have a problem ("Shida") and request assistance. Sending an SMS is inexpensive (less than $0.05); however, in some circumstances where network credit is not available or was impractical, the patients can use the free 'flashback' function to trigger a call from the clinician. The clinician then calls to follow-up and provide triage to any subjects that respond that there is a problem, or subjects who fail to respond within two days.

Clinicians are only expected to respond to text messages during regular clinic hours, but are not restricted to do so. Intervention participants are instructed that the intervention is a clinic utility and that all emergencies should be handled through their usual means such as attending the nearest hospital emergency department. All participants receive a brief training from the clinicians on use of the phone and the protocol if they were in the intervention. Use of any of the cell phone network providers is allowed. Receiving SMS text messages or voice calls in Kenya is free on all networks.

### Control

Patients randomized to the control arm receive their usual standard of care (SOC) clinic support but are not sent the weekly SMS slogans from the clinicians. They are, however, free to call the clinic staff at any time on their own initiative. All cell phone communications between clinicians and study participants, in both study arms, are recorded in a study log.

### Objectives

#### Primary objectives

The study is intended to test whether the cell phone intervention (SMS) improves self-reported adherence to HAART and whether it affects a biological surrogate marker of adherence, specifically suppression of plasma HIV RNA load at 12 months follow-up. We hypothesize that the SMS intervention will remind patients taking HAART about clinic support and reinforce regular communications in order to sort out any adherence related problems efficiently. Thus, we hypothesize the intervention will positively support patients' adherence to HAART and consequent suppression of HIV viral load compared to patients who only receive the standard of care (control).

#### Secondary objectives

We will also test the cell phone intervention (SMS) ability to improve health, quality of life, social, economic outcomes and retention in ART programs. We hypothesize that patients who receive the weekly SMS reminders (intervention) may have improved immune reconstitution (CD4 count), increased body weight, fewer opportunistic infections, fewer adverse health events, improved quality of life, delayed death, improved social factors such as disclosure of their HIV status, and improved economic indicators compared to those that do not receive the intervention (control). We also hypothesize that subjects in the intervention arm will be more frequently retained in the ART program.

### Outcome measures

#### Sampling and enrolment

We determined that continuous sampling was impractical since the clinics are often extremely busy and clinic staff are obliged to provide rapid patient care in order to meet service targets. Only a few patients (typically up to five) can typically undergo the consenting and enrolment evaluation process daily at each site. Subjects are not screened if they are participating in a different adherence study, which occurs at one clinic site. To determine the comparative characteristics of study participants with the general clinic population, we will compare baseline characteristics of a sample of non-study participants with characteristics of subjects enrolled in our study. Since mobile phone access is an enrolment criterion, we will include comparison of baseline characteristics of study enrolees with other clinic attendees who do not have phone access.

#### Primary outcomes

The first primary outcome is patient adherence to HAART at twelve months. (See Appendix) This is assessed by self-report using a standard questionnaire of the number of pills missed in the last 30 days and calculating percent adherence based on the expected number of doses taken. Percent adherence will be analyzed as a continuous variable and dichotomous variable. Subjects are considered either 'adherent' or 'non-adherent' using an optimal adherence cut off of > 95% of medications taken as directed.[1] Adherence is assessed at each follow-up visit and 'ever-non-adherent' will be our dichotomous outcome. The twelve month scheduled follow-up (defined, allowing for non-exact timing of clinic attendance, as follow-up up to 15 months if patients not present at 12 months) is the primary analysis. The six month assessment will allow for evaluating trends but is not the primary outcome.

The second primary outcome is suppression of plasma HIV RNA load at twelve months after initiating ART. If patients are adherent to HAART regimens, absorb the drugs normally, and if their virus is not resistant to the HAART drugs in the regimen, then plasma HIV load should be suppressed to below detectable levels (≤400 copies per ml) by six months and remain suppressed thereafter. Due to variability in when patients show up for scheduled appointments, we accept follow-up on or after 20 weeks as the six month outcome visit. Analysis of 'suppressed' (≤400 copies/ml) versus 'failure' to suppress (>400 copies/ml) at twelve months as a dichotomous variable is the primary analysis. However, decrease in plasma HIV load copies from baseline to twelve month follow-up will also be analyzed as the difference in a continuous variable from baseline to twelve months.

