### Sample size

The primary objectives of this trial to improve adherence to HAART and suppression of HIV viral load evaluated at 12 months. The sample size calculation is based on the comparison between proportions of patients with adherence rates (measured as percent of adherence >95%) in the two groups at 12 months because this is the variable that required the larger sample size. The criterion for significance (alpha) has been set at 0.05. The test is 2-tailed, which means that an effect in either direction will be interpreted.

The sample was calculated using (Cary, NC). With the proposed sample size of 247 and 247 for the two groups (ie assuming a 1:1 allocation ratio), the study will have power of 80% to yield a statistically significant result using a chi-squared test (assuming an intention-to-treat principle for the analysis) at alpha = 0.05/2 (ie using the Bonferroni correction factor for the two primary outcomes).

This computation assumes 10% improvement in 'perfect adherence' over a baseline of 75% determined from rates in a large adherence trial by AMPATH in Western Kenya which we felt is the most representative data available. [7] This difference of 10% was selected as the smallest difference that would be important to detect, in the sense that any smaller difference would not be of clinical or substantive importance. It is also assumed that this difference is reasonable, in the sense that an effect of this magnitude could be anticipated in this field of research.

Assuming attrition rates of approximately 10% we intend to over-enrol by 10% resulting in an enrolment target of at least 534 participants for randomization (267 in the Intervention, and 267 in the Control).

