#### Statistical methods

The intervention arm (SMS) will be compared against the control (SOC) for all primary analysis. We will use chi-squared test for binary outcomes, and T-test for continuous outcomes. For subgroup analyses, we will use regression methods with appropriate interaction terms (respective subgroup × treatment group). Multivariable analyses will be based on logistic regression (See Table 2) for binary outcomes and linear regression for continuous outcomes. We will examine the residual to assess model assumptions and goodness-of-fit. For timed endpoints such as mortality we will use the Kaplan-Meier survival analysis followed by multivariable Cox proportional hazards model for adjusting for baseline variables. We will calculate Relative Risk (RR) and RR Reductions (RRR) with corresponding 95% confidence intervals to compare dichotomous variables, and difference in means will be used for additional analysis of continuous variables. P-values will be reported to four decimal places with p-values less than 0.001 reported as p < 0.001. Up-to-date versions of SAS (Cary, NC) and SPSS (Chicago, IL) will be used to conduct analyses. For all tests, we will use 2-sided p-values with alpha = < 0.05 level of significance. We will use the Bonferroni method to appropriately adjust the overall level of significance for multiple primary outcomes, and secondary outcomes.

To assess the impact of potential clustering for patients cared by the same clinic, we will use generalized estimating equations [GEE] (ref) assuming an exchangeable correlation structure. Table 3 provides a summary of methods of analysis for each variable. Professional academic statisticians ([name]) blinded to study groups will conduct all analyses.

**Table 3 T3:** Variables, Measures and Methods of Analysis

**Variable/Outcome**	**Hypothesis**	**Outcome Measure**	**Methods of Analysis**
1) **Primary**	Intervention improved outcome from baseline to 6 months		
			
a) Adherence at 12 months		Percent adherence in previous 30 days >95% [binary]	Chi-squared test
			
b) Suppression of HIV viral load at 12 months		Viral load ≤400 copies/ml [binary]	Chi-squared test

2) **Secondary** Adherence percentage at 12 months	improvement occurred	Adherence % (>95%) [binary]	Chi-squared test

HIV viral load at 12 months	improvement occurred	Viral load (copies)	T-test

Immune reconstitution (change in CD4 T cell count from baseline)	improvement occurred	Cd4 T-cells/mm^3 ^(continuous)	T-test

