## Appendix

### Primary Outcome Measures

HAART = highly active antiretroviral therapy.

Primary binary outcomes (12 months post initiation of HAART)

1. Self-reported adherence (>95%) in previous 30 days)

2. Suppressed HIV viral load (≤400 copies/ml)

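### The first primary outcome has two incompatible binary definitions: adherent at month 12, and ever non-adherent over the month-6 and month-12 visits

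*Protocol article*

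**What the plan says.** All references are to the protocol article.

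- **Primary outcomes, opening sentence:** "The first primary outcome is patient adherence to HAART at twelve months". It is measured by self-report of pills missed in the last 30 days and dichotomised at more than 95%.
- **Same paragraph, on the binary variable:** "Adherence is assessed at each follow-up visit and 'ever-non-adherent' will be our dichotomous outcome". Follow-up visits are at 6 and 12 months.
- **Same paragraph, two sentences later:** "The six month assessment will allow for evaluating trends but is not the primary outcome". The sentence in between makes the twelve-month follow-up, with a window to 15 months, the primary analysis.
- **Sample size:** the calculation compares proportions above 95% adherence "in the two groups at 12 months because this is the variable that required the larger sample size". The rates come from this statement: "This computation assumes 10% improvement in 'perfect adherence' over a baseline of 75" per cent.
- **Table 3, row (a), labelled as adherence at 12 months:** "Percent adherence in previous 30 days >95% [binary", tested by chi-squared.
- **Appendix, under outcomes at 12 months after starting HAART:** "Self-reported adherence (>95%) in previous 30 days".
- **Table 3, hypothesis cell for the primary outcomes:** "Intervention improved outcome from baseline to 6 months".
- **Analysis of primary and secondary outcomes:** a general rule counts missing outcome data as treatment failures. It is then spelled out for month 12 only.

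**The concern.** A variable that records whether a patient was ever non-adherent makes a month-6 failure a primary failure. That cannot be squared with a primary outcome at twelve months in which month 6 serves only to show trends. Nor can the sentence be read as the month-12 variable under another name: it refers to every follow-up visit, and 'ever' adds nothing to a single 30-day recall.

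The two versions have different event rates and respond differently to the timing of an effect, so they can give different answers. The outcome is self-reported, the questionnaires are administered by clinic staff, and the trial is open-label. In that setting the primary variable should leave no choice open once data exist. The sample size was worked out for only one of the two versions.

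**Working it through.** **1. The texts side by side**

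| Adherent at month 6 | Adherent at month 12 | Month-12 rule | 'Ever' rule |
|---|---|---|---|
| yes | yes | success | success |
| no | yes | **success** | **failure** |
| yes | no | failure | failure |
| no | no | failure | failure |

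The rules differ in exactly one pattern: non-adherent at month 6, adherent at month 12.

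**2. The plan's own figure**

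Stated inputs: 75% against 85% (10% read as percentage points), two-sided test, 80% power, alpha 0.05/2 = 0.025, 247 per arm. These rates are for the month-12 binary.

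The unpooled formula is n = [p1(1−p1) + p2(1−p2)] × (z for alpha + z for power)² / d², with 0.1875 + 0.1275 = 0.315 and d = 0.10. It gives 247.2 per arm at two-sided 0.05 and 299.4 at two-sided 0.025. The pooled chi-squared formula gives 250 and 303. So 247 is reproduced only without the Bonferroni split. That is a separate matter, but it sets the comparator.

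Power by the pooled formula is Φ{[d√n − z√(2p̄(1−p̄))] / √(p1(1−p1) + p2(1−p2))}. With n = 247, z = 2.2414 and p̄ = 0.80:

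- d√n = 0.10 × 15.716 = 1.572
- z√0.32 = 1.268
- (1.572 − 1.268) / √0.315 = 0.541
- Φ(0.541) = 0.706

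The month-12 binary therefore has about 71% power at two-sided 0.025 (79.5% at 0.05).

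**3. The 'ever' version**

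The protocol gives no rate for it. Two assumptions are needed, neither of which it supplies for this endpoint: 75% of controls adherent at each visit, and a between-visit correlation ρ of 0.2 to 0.6.

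- P(adherent at both visits) = p6·p12 + ρ√[p6(1−p6)·p12(1−p12)].
- Control: 0.5625 + 0.1875ρ.
- Share of controls classified differently: 0.75 − P(both) = 0.1875(1−ρ).
- SMS arm, gain at both visits (85% and 85%): 0.7225 + 0.1275ρ.
- SMS arm, gain at month 12 only (75% and 85%): 0.6375 + 0.1546ρ.

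Results with 247 per arm at two-sided 0.025:

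| ρ | Control, never non-adherent | Classified differently | SMS, gain at both | Power | SMS, gain at month 12 only | Power |
|---|---|---|---|---|---|---|
| 0.2 | 60.0% | 15.0% | 74.8% | 90% | 66.8% | 25% |
| 0.4 | 63.75% | 11.25% | 77.35% | 86% | 69.9% | 22% |
| 0.6 | 67.5% | 7.5% | 79.9% | 82% | 73.0% | 18% |

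**4. Type I error if either version could be declared primary**

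Under no effect, the two test statistics have the correlation of the two binary variables: r = P(both)(1−0.75) / √[P(both)(1−P(both)) × 0.1875]. This is 0.71, 0.77 and 0.83 for ρ = 0.2, 0.4 and 0.6. The probability that at least one of two standard normal statistics with that correlation exceeds 2.2414 in absolute value is 0.043, 0.041 and 0.039, against a nominal 0.025.

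**The case against.** The strongest reply is that the document leans heavily one way. The abstract, the primary objectives, the sample size, Table 3 row (a) and the Appendix all place the endpoint at twelve months, and one sentence dissents. That is true, and it shows which version to keep. It does not remove the conflict: the dissenting sentence stands in the section that defines the outcome, and it is the one that names the dichotomous variable.

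Four stronger readings are tempting but not supported.

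- *That the primary test is open.* The chi-squared test is named in both Sample size and Table 3. Only its input variable is in doubt.
- *That Table 3 gives a third definition, and one impossible for adherence.* The month-6 wording is a hypothesis cell over rows labelled 12 months. It covers both primary outcomes, and viral load does have a baseline. It is a timing slip.
- *That a missed month-6 visit has no rule.* The general missing-as-failure rule can be read to cover it. At most, its application to month 6 is not spelled out.
- *That the 'ever' version would ruin an 80% design.* On the same inputs the month-12 version has about 71% power, and 'ever' does better if the gain is present at both visits. The 18% to 25% requires no effect at all at month 6, which messages sent every week do not suggest.

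The article also says that statisticians blinded to study group will do the analyses. That lowers the risk of a selective choice but does not settle which variable is primary. The type I error figure applies only if both versions are tested and the better one is reported; nothing in the document says this is intended.

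**Conclusion.** The concern holds as a stated contradiction in a primary endpoint. It is not detail that an article may leave to a fuller document. Two binary versions of the first primary outcome are given, and they classify some patients oppositely.

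The size is illustrative, because the per-visit rate and the between-visit correlation are assumptions. On those assumptions 7.5% to 15% of controls change category. Power for the cumulative version could be well above or well below that of the month-12 version, depending on when the effect appears. An open choice between the two would raise the type I error for this outcome from 0.025 to about 0.04. The contradiction itself rests on no assumption. It should be resolved before any outcome data are analysed.

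**What to change.** 1. In Primary outcomes, state one primary binary variable: more than 95% adherence in the previous 30 days at the 12-month visit (window to 15 months), with missing counted as non-adherent. Sample size, Table 3 row (a) and the Appendix already agree with this.
2. Move 'ever-non-adherent' (month 6 or month 12) to the secondary outcomes, and state how the missing-as-failure rule applies to a missed month-6 visit.
3. In Table 3, replace the month-6 primary hypothesis with a comparison of SMS against standard of care at 12 months.
4. As a minor labelling correction, make the secondary adherence row of Table 3 continuous. It now repeats the binary primary, whereas Primary outcomes also intends percent adherence as a continuous variable.

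The cost is protocol wording only. No new data are needed, and the variable used for the sample size does not change.

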#### Secondary outcomes

The potential benefits of the intervention are quite broad, so multiple secondary outcomes are of interest and were selected through academic collaboration. The secondary outcomes fall under the categories of health, quality of life, social factors, and economic indicators (see Table 1). The primary purpose of taking antiretroviral medications for HIV infection is to maintain or restore health in someone who is HIV infected. Several other factors that contribute to a subject's prosperity or overall well-being may be affected directly (by way of enhanced support mechanisms associated with the intervention), or indirectly (through improvements in health related to HAART effect). We therefore feel it is important to assess each of these outcomes independently.

**Table 1 T1:** Secondary Outcome Measures

**Secondary outcome measures (6 months and 12 months post initiation of HAART)**	**Type**
*Health outcomes*	
Self-reported adherence as a percentage	Binary
Suppressed HIV viral load (in copies)	Continuous
Immune reconstitution (change in CD4 T cell count from baseline)	
Time to virological failure	Continuous
Weight gain [lbs] and BMI	Time-to-event
Occurrence of opportunistic infections (OIs)	Continuous
Time to reporting of adverse drug events (ADEs)	Binary
Deaths (all cause)	Time-to-event
*Quality of life (QOL)*	Time-to-event
SF-12	
Satisfaction with care provided	Continuous
*Social factors*	Continuous
Level of disclosure of HIV status	
Impression of stigma	Binary
Family dyamics	Continuous
*Economic factors*	Continuous
Employment attendance	
Household member school attendance	Continuous
Cell phones lost/stolen	Continuous

HAART = highly active antiretroviral therapy, SF-12 = short form 12 adapted for regional application in Kiswahili.

In addition, we hypothesize that the intervention will lead to improved retention on ART.[5] Because participants are actively traced for twelve month follow-up visits, we will use composite retention outcomes. We define 'retained' as someone who followed-up on their scheduled visit without being traced and is still taking ART versus 'unretained' which includes subjects who stopped taking ART before their twelve month visit, who are lost to follow-up, or required active tracing after missing their scheduled twelve month appointment. We will report each element of the composite endpoints.[6]

### Sample size

The primary objectives of this trial to improve adherence to HAART and suppression of HIV viral load evaluated at 12 months. The sample size calculation is based on the comparison between proportions of patients with adherence rates (measured as percent of adherence >95%) in the two groups at 12 months because this is the variable that required the larger sample size. The criterion for significance (alpha) has been set at 0.05. The test is 2-tailed, which means that an effect in either direction will be interpreted.

The sample was calculated using (Cary, NC). With the proposed sample size of 247 and 247 for the two groups (ie assuming a 1:1 allocation ratio), the study will have power of 80% to yield a statistically significant result using a chi-squared test (assuming an intention-to-treat principle for the analysis) at alpha = 0.05/2 (ie using the Bonferroni correction factor for the two primary outcomes).

This computation assumes 10% improvement in 'perfect adherence' over a baseline of 75% determined from rates in a large adherence trial by AMPATH in Western Kenya which we felt is the most representative data available. [7] This difference of 10% was selected as the smallest difference that would be important to detect, in the sense that any smaller difference would not be of clinical or substantive importance. It is also assumed that this difference is reasonable, in the sense that an effect of this magnitude could be anticipated in this field of research.

Assuming attrition rates of approximately 10% we intend to over-enrol by 10% resulting in an enrolment target of at least 534 participants for randomization (267 in the Intervention, and 267 in the Control).

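### The stated 80% power does not hold at the Bonferroni level of 0.025: 247 per arm is the sample size for an unadjusted 0.05, and power at 0.025 is about 71%

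*Protocol article*

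**What the plan says.** The Sample size section of the protocol article sizes the trial on the proportion of patients with adherence above 95% at 12 months, the primary outcome said to need the larger sample. It assumes 75% in controls and a 10% improvement.

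- Overall level: "The criterion for significance (alpha) has been set at 0.05".
- Sidedness: "The test is 2-tailed, which means that an effect in either direction will be interpreted".
- Size: "With the proposed sample size of 247 and 247 for the two groups".
- Claim: "the study will have power of 80% to yield a statistically significant result using a chi-squared test".
- Level for that claim: "at alpha = 0.05/2 (ie using the Bonferroni correction factor for the two primary outcomes".

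Enrolment is then raised to 267 per arm (534 in total) for attrition of about 10%. Statistical methods confirms that Bonferroni will be applied across the primary outcomes. It also says that relative risks will be reported "with corresponding 95% confidence intervals to compare dichotomous variables".

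**The concern.** The section gives a sample size, a power, an effect and a significance level, and any three of these determine the fourth. Here they do not agree. The figure of 247 is what the usual formula gives for 75% against 85% at 80% power with an unadjusted two-sided 0.05. Splitting alpha between two primary outcomes must cost either patients or power, and the plan shows neither cost.

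Adherence sets the size of the trial, and the plan calls 10 points the smallest difference of clinical importance. If power is overstated, a non-significant adherence result would be read as coming from a design with a 20% miss rate under multiplicity control, when the rate is nearer 29%.

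A smaller mismatch follows from the same split. If each primary is tested at 0.025 but reported with a 95% interval, a result with a p-value between 0.025 and 0.05 will usually have an interval that excludes no effect although the test does not reject.

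**Working it through.** **Inputs** (all from Sample size): p1 = 0.75, p2 = 0.85, difference 0.10, 1:1 allocation, n = 247 per arm, two-sided chi-squared test, alpha = 0.05/2 = 0.025, target power 80%.

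Normal quantiles: 1.960 (two-sided 0.05), 2.241 (two-sided 0.025), 0.842 (80% power).

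Variance terms: 0.75×0.25 + 0.85×0.15 = 0.315 (unpooled); 2×0.80×0.20 = 0.32 (pooled).

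**Step 1. Reproduce 247.** Unpooled formula: n = (z_alpha + z_power)² × 0.315 / 0.10².

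- At 0.05: (1.960 + 0.842)² × 31.5 = **247.2**
- At 0.025: (2.241 + 0.842)² × 31.5 = **299.4**, so 300

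The arcsine formula gives 247.6 and 299.8. The pooled formula, n = [z_alpha√0.32 + z_power√0.315]² / 0.10², gives 250.0 and 302.9. The plan's 247 therefore matches the calculation at 0.05.

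**Step 2. Power at 247 per arm.**

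Unpooled: standard error = √(0.315/247) = 0.03571 and 0.10/0.03571 = 2.800.

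- At 0.05: Φ(2.800 − 1.960) = Φ(0.840) = 80.0%
- At 0.025: Φ(2.800 − 2.241) = Φ(0.559) = 71.2%

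Pooled: null standard error = √(0.32/247) = 0.03599.

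- At 0.05: Φ((0.10 − 1.960×0.03599)/0.03571) = 79.5%
- At 0.025: Φ((0.10 − 2.241×0.03599)/0.03571) = 70.6%

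| Method, n = 247 per arm | Two-sided 0.05 | Two-sided 0.025 |
|---|---|---|
| Unpooled | 80.0% | 71.2% |
| Arcsine | 79.9% | 71.1% |
| Pooled | 79.5% | 70.6% |
| Exact enumeration of the chi-squared test | 79.7% | 70.9% |
| Simulation, 400,000 trials | 79.8% | 71.0% |

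The methods differ by less than 1 point; the gap from the stated 80% is about 9.

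**Step 3. Other readings.**

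- *One-sided 0.025* equals two-sided 0.05 and would reproduce 247. The text excludes it: the test is 2-tailed and the halving is attributed to the two primary outcomes.
- *A relative 10% improvement* (75% to 82.5%) gives 41.9% power at 0.025.
- *A continuity correction* raises the requirement at 0.025 to 323 per arm.
- *All 267 per arm analysed, rates unchanged*, gives 74.3% (pooled) or 74.6% (exact) at 0.025.

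**Step 4. What 247 per arm can detect.** At two-sided 0.025 and 80% power, the detectable difference from 75% is about 11.0 points, not 10.

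**The case against.** The arithmetic is not in dispute. The case on the other side concerns how far the point reaches, and much of it stands.

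- **Cause.** The article shows no formula. That the correction was named but never entered is the likely explanation, since 247 matches the uncorrected result, but the text proves only that size, power and alpha disagree.
- **Consequence.** The 29% miss rate is for adherence alone. Nothing requires both primaries to succeed, so the chance that at least one is significant may be higher. No estimate is biased, and Bonferroni at analysis still controls the type I error.
- **Confidence intervals.** A 95% interval beside an adjusted test is common practice and not an arithmetic error. This is a lesser matter.
- **Holm.** Bonferroni is valid, and Holm's gain depends on the viral-load outcome. In simulation, adherence power rises from 71% to 76–77% if both outcomes have similar effects (assumed correlation 0.2 to 0.6), to 73–74% if the mean z-statistic for viral load is about 2, and stays at 71% if viral load shows no effect. It never reaches 80% in these cases.
- **Analysis population.** The Analysis plan counts missing 12-month outcomes as failures among all randomised, so 247 completers are not the planned analysis set. If 75% and 85% already count losses as failures, power with 267 per arm is about 74%. If they apply to completers and 10% are missing in each arm (an assumption), the rates become 0.9×75% = 67.5% and 0.9×85% = 76.5%, and power is about 53% at 0.025. The article does not say which is meant. This limits what the 71% describes, but neither version rescues the stated 80%.

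**Conclusion.** The concern holds and must be fixed. On the protocol's own inputs, power at two-sided 0.025 with 247 per arm is about 71%, not 80%. The stated size delivers 80% only without the Bonferroni correction, and 80% at 0.025 needs 300 to 303 analysed per arm. The over-enrolment to 267 does not close the gap.

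The result rests on reading the improvement as 75% to 85% absolute and the test as two-sided, as the text has it. The 71% applies to 247 analysed patients per arm with those rates; under the planned missing-as-failure analysis the figure is about 74%, or about 53% if the rates describe completers and 10% are lost from each arm.

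**What to change.** **Required.** Correct the power statement in Sample size, for example:

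> With 247 patients analysed per arm, a two-sided chi-squared test of 75% against 85% has about 71% power at alpha 0.025 (80% at alpha 0.05).

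Add whether 75% and 85% count missing outcomes as failures, and give the power for the 267 per arm who enter the intention-to-treat analysis on that basis.

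**Optional.**

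- Replace Bonferroni by Holm for the two primary outcomes, fixed before any comparison by arm. The smaller p-value is tested at 0.025 and, if significant, the other at 0.05. The family-wise error is the same, and per-outcome power rises to about 77% if both effects are similar, with no loss otherwise.
- Report 97.5% intervals for the two primary outcomes. These match the Bonferroni level. Under Holm, an outcome significant only at the second step can have a 97.5% interval that includes no effect, and the report should say so.

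**Cost.** Wording only and no additional patients; the stated power becomes less favourable. Restoring 80% at a Bonferroni 0.025 would instead take 53 to 56 more analysed patients per arm, before any allowance for losses.
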